### Who will be included in each analysis {27b}

The primary analyses will follow the intention-to-treat (ITT) principle, including all randomized participants in the groups to which they were originally allocated, irrespective of intervention completion or follow-up attendance. In addition, per-protocol analyses will be conducted as a secondary analyses, including only participants who complete all six intervention sessions and all follow-up sessions.

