### Outcomes {16}

#### Study instruments for primary outcomes

The Overt Aggression Scale‐Modified [29, 30] is a semi-structured interview designed to evaluate various categories of aggressive behaviors. Four sub-components make up the overall aggression (AGG) score: Verbal Aggression, Aggression Against Object, Aggression Against Others, and Aggression Against Self. Subcomponent scores are determined by multiplying the number and severity level of aggressive behaviors of each type during the prior week. Additional scores include a Global Anger and Aggression (GAA) score composed of two item ratings: Subjective experience of anger and overt expression of anger. The OAS‐M has been shown to be reliable and valid, with good psychometric properties in terms of internal consistency, inter-rater reliability, test–retest reliability, face validity, convergent validity, divergent validity, and discriminant validity [30]. The primary outcome of the study will be the change in overall aggression score from baseline to the 1-Month post-intervention follow-up, as measured using the Overt Aggression Scale–Modified (OAS-M), and will be summarized using mean values and standard deviations.

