Subsequently, the experimental and control group participants will undergo the inhibitory control training or sham training for 3 consecutive days, respectively, administered by the primary investigator (psychologist) for all patients. Throughout this period, the study participants will continue to receive concurrent treatment as usual as per the advice of the clinical treating team. Any changes in the medication that occur during the study period will be recorded.

One day after the intervention, participants will be assessed using the outcome measure administered during the baseline assessment. The first follow-up will be held at 1 month post-intervention (± 4 Days), and the second follow-up will be held at 3 months post-intervention (± 7). A comprehensive record of treatment prescribed to the participants will be maintained throughout the study period. After the final follow-up, participants will be prompted to guess their allocation group, either control or experimental, which will aid in assessing the effectiveness of the trial's blinding. They will also be asked about their perception of whether the intervention they received influenced their levels of aggression. The instrument administration and study timeline has been summarized in Fig. 3.

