#### Sample size {19}

Drawing upon findings from Khan et al. [45], patients exhibited a significant reduction in aggression from a mean of 3.44 (SD = 3.89) to 1.07 (SD = 1.92) on the Overt Aggression Scale—Modified (OAS-M) after the computerized cognitive and social cognition training. The effect size was calculated using the G*Power software (Version 3.1.9.6) with a priori power analysis for a t-test comparing two dependent means (matched pairs) and an assumed correlation of 0.5 between paired measurements [46]. A paired t-test framework was used for effect size estimation because the control group (sham training) in this study serves primarily as a means of studying the mechanism of work of the ICT (i.e., 100% contingency-based associative learning), due to which we employed only 50% contingency between aggressive stimuli and no-go responses in the ST, which as suggested by some of the past literature, opposes how the ICT works [20, 23, 24]. However, recent studies have reported comparable effectiveness of sham and active inhibitory control training, raising uncertainty regarding the specificity of the proposed mechanism [47]. Similar concerns have also been raised in relation to attentional bias modification interventions, which were previously assumed to operate through similar mechanisms but have more recently been shown to give non-specific effects [48]. Therefore, to estimate the expected magnitude of change attributable to inhibitory control training itself, pre–post scores from the experimental condition were used for effect size calculation from prior literature.

According to the above estimates based on the prior literature, with a corresponding effect size of 0.70, power of 80%, and alpha of 0.05, the necessary sample size required to detect a comes out to be at least 26 subjects in each group (i.e., experimental and control) [49].

As per another study conducted at the same tertiary care centre as the current study [50], the dropout rate among patients was about 45% at 1 month, and another 15% increase in dropouts was reported at the 3-month follow-up. Thus, assuming a planned attrition rate of 60% in both groups using this reference, the overall required sample size for the research study is recalculated to 130 participants, with 65 participants in each group.

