## Statistical methods

### Statistical methods for primary and secondary outcomes {27a}

Initial analyses will summarize demographic and clinical data of the participants using descriptive statistics. Mean values and standard deviations will be used to describe baseline and outcome variables for the experimental as well as for the control condition across all assessment times. Prior to further analyses, t-tests (or equivalent non-parametric tests) will be applied to confirm equivalence between both groups in demographic characteristics and pre-intervention scores. Any initial differences will be considered for adjustment in subsequent analyses. Based on the normality of the data, parametric or equivalent non-parametric tests will be conducted to assess the differential effects of the intervention training compared to the sham training on each outcome variable over time. The primary outcome, overt aggression measured using the Overt Aggression Scale – Modified (OAS-M), will be analysed with time (baseline, 1-day post-intervention, 1-month post-intervention, and 3-month post-intervention) as the within-subjects factor and group (inhibitory control training vs sham training) as the between-subjects factor.

Secondary continuous outcomes will also be analysed using similar models. Outcomes expressed as categorical or binary variables (e.g., substance use or gambling presence) will be summarised as frequencies and proportions and analysed using appropriate analysis methods. All statistical analysis methds wil onl;y be decided upon once its ensures that our collected data meets the assumptions of the respective test. Harms will be reported descriptively.

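### The secondary per-protocol set requires the 3-month visit although the primary endpoint is complete at 1 month, which makes it a completer set

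*Protocol article*

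**What the plan says.** All references are to the Protocol article.

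- *Who will be included in each analysis {27b}*: the primary analyses are intention-to-treat and keep every randomised participant, whatever sessions or visits he attended. Beside them, "per-protocol analyses will be conducted as a secondary analyses", "including only participants who complete all six intervention sessions and all follow-up sessions". The same rule covers all per-protocol analyses. No set specific to an endpoint or time point is given here or elsewhere in the article.
- *Study instruments for primary outcomes*, under Outcomes {16}: "The primary outcome of the study will be the change in overall aggression score from baseline to the 1-Month post-intervention follow-up", measured on the OAS-M.
- *Participant timeline {18}*: after the 1-month visit, "the second follow-up will be held at 3 months post-intervention".
- *Sample size {19}*: in an earlier study at the same centre, "the dropout rate among patients was about 45% at 1 month, and another 15% increase in dropouts was reported at the 3-month follow-up". The protocol then inflates its sample size "assuming a planned attrition rate of 60% in both groups".
- *Protocol and statistical analysis plan {5}*: the analysis plan is described as integrated in the protocol, so the {27b} rule is the stated rule and not a placeholder.

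**The concern.** A per-protocol analysis is meant to describe the comparison among participants who received the allocated training as planned. Training here lasts three days and the primary endpoint is measured at 1 month. Whether a man returns at 3 months says nothing about whether he received the training, and it happens after the endpoint has been observed. Conditioning on it turns the per-protocol set into a set of study completers.

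Two things are at stake, both confined to the secondary analysis:

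- **Precision.** Observed 1-month outcomes from fully trained men are set aside.
- **Selection.** Membership depends on an event after the endpoint. The protocol's background section treats inhibitory control, aggression and addictive behaviour as one interacting cycle, so it is plausible that later attendance is related to outcome. The protocol gives no data on this.

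The per-protocol result may also draw more attention than usual. Heavy attrition is expected by 1 month, and the choice of imputation method is left until data collection is complete ({27c}).

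**Working it through.** **Inputs** (all from Sample size {19}): 65 randomised per arm, 130 in total; "at least 26 subjects in each group" required before inflation; dropout of 45% at 1 month and a further 15% by 3 months; planned total attrition of 60%.

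**Step 1. Reproduce the plan's figure.** 26 / (1 − 0.60) = 65 per arm, 130 in total. This matches. The protocol adds its two dropout figures, 45% + 15% = 60%, so 60% is the attrition at 3 months.

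**Step 2. Participants with a 1-month outcome.** 65 × (1 − 0.45) = 35.75, about 36 per arm (71.5 in total).

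**Step 3. Participants who can meet the all-visits rule.** 65 × (1 − 0.60) = 26 per arm (52 in total).

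**Step 4. Loss due to the 3-month requirement.** 35.75 − 26 = 9.75, about 10 per arm (19.5 in total). As a share of those with an observed primary outcome: 9.75 / 35.75 = 27.3%.

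**Step 5. Effect on precision.** With the same standard deviation and equal arms, the standard error of a two-group difference scales with 1/√n. The ratio is √(35.75 / 26) = 1.17, a rise of about 17%.

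**Step 6. Sensitivity to the reading of the 15%.** If the further 15% is taken as a share of those still in the study at 1 month, 3-month retention is 0.55 × 0.85 = 0.4675.

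| Reading | 1 month, per arm | 3 months, per arm | Dropped per arm | Share dropped | Rise in standard error |
|---|---|---|---|---|---|
| Additive (60% total) | 35.75 | 26.0 | 9.75 | 27% | 17% |
| Share of those remaining | 35.75 | 30.4 | 5.4 | 15% | 8% |

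The second reading implies total attrition of 1 − 0.4675 = 53%, which is not the protocol's 60%. The additive reading is therefore the protocol's own.

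**Assumptions.** Dropout is monotone, so that everyone seen at 3 months was also seen at 1 month. Completion of the six sessions is unrelated to later attendance. The set sizes of 36 and 26 are upper limits, because some men seen at follow-up may not have completed all sessions.

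**The case against.** **The main inference does not depend on this set.** This stands in full. A reader might infer that the rule removes participants from the trial's primary result. It does not: under {27b}, a man with a 1-month score who misses month 3 stays in the intention-to-treat analysis.

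**The rule fits the stated model.** Section {27a} analyses OAS-M with "time (baseline, 1-day post-intervention, 1-month post-intervention, and 3-month post-intervention) as the within-subjects factor". A classical repeated-measures analysis would need every visit, so one completer set for all outcomes would be coherent. This stands only in part. Section {27a} leaves the method open, and a change from baseline to 1 month needs only two measurements.

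**The set keeps its planned size.** The 26 per arm is the number that the sample size section aimed to have evaluable after 60% attrition. That is correct, so the loss is relative to the data that will be available and not to the design target. It is still a loss of observed outcomes for no analytic gain at 1 month.

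**Bias is asserted, not shown.** This stands. A reader might infer that the per-protocol estimate will be biased in a known direction. The protocol gives no evidence on how 3-month attendance relates to outcome and plans for equal attrition in both arms. Selection is a possibility of unknown size and direction.

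**The remedy also conditions on attendance.** This stands too. By 1 month, 65 − 35.75 = 29.25 per arm are already expected to be lost, against 9.75 more by month 3. A reader might infer that the revised set would give the effect in everyone who received the training. It would give it in trained men who returned at 1 month.

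**The current wording is clear and fixed in advance.** It is, and it contradicts nothing. The criticism is that it is a poor choice for this endpoint, not that it is ambiguous.

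**Conclusion.** The point holds as a limited criticism of a secondary analysis. The per-protocol rule in {27b} selects on retention two months beyond the primary endpoint and so defines a completer set. On the protocol's additive attrition figures, it discards about 27% of observed 1-month outcomes among potential members (15% on the less natural reading) and raises the standard error by about 17% (8%). These figures rest on monotone dropout, on session completion being unrelated to attendance, and on dropout rates taken from a study that is cited but not shown. Added selection bias is possible but not quantified. The primary intention-to-treat inference is unaffected. The change is worth making because it is cheap and uses data that will be collected anyway.

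**What to change.** Amend {27b} so that the set follows the endpoint:

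- For the 1-month primary endpoint, the per-protocol set consists of participants who completed all six sessions and have both baseline and 1-month OAS-M scores.
- The 3-month visit is required only for per-protocol analyses of 3-month outcomes.
- State that this recovers observed data and removes selection on the later visit, but that selection on 1-month attendance remains.

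The cost is a short change of wording through the protocol's amendment route ({31}), made before analysis. No new data are needed. The per-protocol sample will differ between the 1-month and 3-month analyses, so the number in each should be reported.

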### How missing data will be handled in the analysis {27c}

The method of data imputation will be chosen based on the characteristics and nature of the missing data following completion of data collection, ensuring appropriate handling of any incomplete data points.

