### Methods for additional analyses (e.g. subgroup analyses) {27d}

After the completion of data collection, the data will be reviewed for suitability of the following analyses: Post hoc comparisons may be conducted for detailed analysis through between group and within group measures in case prior statistical analysis indicates significant differences. The moderating effect of changes in inhibitory control and stimulus devaluation immediately post intervention on changes in overt aggression behaviours at 1-month and 3-months post-intervention may be analysed.

The moderating effect of changes in inhibitory control and aggressive behaviour immediately following the intervention and at 1-month post-intervention on changes in substance use frequency and gambling behaviour at 1-month and 3-months post-intervention may be analysed.

If a significant dropout rate occurs during the study, an analysis can be conducted to identify any patterns or trends in the characteristics of participants who dropped out. This analysis can help understand potential reasons for dropout in terms of demographic, clinical, or other factors associated with higher dropout rates.

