### Protocol and statistical analysis plan {5}

The full trial protocol, including the statistical analysis plan, is being submitted for publication and will be publicly accessible upon publication. The statistical analysis plan is integrated within the protocol document. The same data will also be available the Clinical Trials Registry of India (CTRI). Any substantive deviations from the pre-specified analysis plan will be clearly documented and justified in subsequent publications.

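### The method for handling missing data is to be chosen after data collection, with the trial's only analyst unblinded and about 45% of the primary outcome expected to be missing; no analysis under informative dropout is stated

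*Protocol article*

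**What the plan says.** - **Missing data, section {27c}.** One sentence, with no method, assumption or fallback named: "The method of data imputation will be chosen based on the characteristics and nature of the missing data following completion of data collection".
- **Primary outcome, section {16}.** "The primary outcome of the study will be the change in overall aggression score from baseline to the 1-Month post-intervention follow-up", measured by the OAS-M.
- **Expected loss, section {19}.** In an earlier study at the same centre, "the dropout rate among patients was about 45% at 1 month, and another 15% increase in dropouts was reported at the 3-month follow-up". The sample size is set "assuming a planned attrition rate of 60% in both groups".
- **Analysis set, section {27b}.** The primary analysis covers everyone randomized, whether or not they attend follow-up. A per-protocol analysis of participants who complete all sessions and all follow-ups is secondary.
- **Dropout analysis, section {27d}.** "If a significant dropout rate occurs during the study, an analysis can be conducted", aimed at the characteristics of those who left.
- **Who analyses, section {24a}.** A single investigator enrols, treats, assesses and analyses, and knows the allocation.
- **Where the analysis plan is, section {5}.** "The statistical analysis plan is integrated within the protocol document".

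**The concern.** An analysis of all randomized participants with close to half the endpoint unobserved depends on how the unobserved part is handled. Here that step is fixed only as something to decide once the data are in. The person who will run the analysis knows the allocation and has rated the outcome. Section {27a} also leaves the statistical tests open until the data have been checked, so no fixed primary model supplies a missing-data assumption by default.

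Two things are at stake. First, the methods that {27c} leaves open differ in error rate and in the size of the effect they report, so a choice made after seeing the data has no protected error rate. Second, the collected data can show how much is missing, when, in whom and in which arm. They cannot show whether dropout depends on the score that was not seen, for example if patients who relapse and become aggressive do not return. Only a sensitivity analysis that varies this assumption can address it, and none is stated.

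**Working it through.** **Inputs from the protocol.** 65 per arm, 130 in total; dropout of about 45% at 1 month plus a further 15% by 3 months (section {19}); primary time point 1 month (section {16}); all randomized participants analysed (section {27b}).

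**The plan's own figure.** 45% + 15% = 60%. 26 / (1 − 0.60) = 65 per arm, and 2 × 65 = 130. This reproduces. The inflation protects the number of completers. It does nothing about bias from who completes.

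**Expected missing scores.**
- 1 month: 65 × 0.45 = 29.25 per arm, leaving about 36; 58.5 of 130 overall.
- 3 months: 65 × 0.60 = 39 per arm, leaving 26; 78 of 130 overall.

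**How far the method matters (illustration).** These assumptions are the reviewer's, not the protocol's: 65 per arm, 45% missing at random in both arms, normal scores in SD units, correlation 0.5 between baseline and 1 month, two-sided 5% t-test on change scores, no true effect.

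| Method | Trials rejecting |
|---|---|
| Complete cases | about 5% |
| Baseline carried forward | about 5% |
| Single regression imputation, fitted on both arms pooled | about 5% |
| Single regression imputation, fitted within arm | about 22% |
| Single mean imputation by arm | about 30% |

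A hand check on the last row: filling with the arm mean makes the reported variance of an arm mean about 0.55 s²/65, while the true variance is s²/36. The standard error is too small by √(65 / (36 × 0.55)) = 1.81. The effective critical value is 1.96 / 1.81 = 1.08, which gives a two-sided rejection rate of about 28%.

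The within-arm regression figure depends on the test. With baseline-adjusted ANCOVA in place of the change-score test it is about 29%. Skewed scores gave the same pattern: 22% for change scores, 31% for ANCOVA, and 4% to 5% when fitted on pooled arms.

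**Size of the estimate.** With a true effect of 0.70 SD, baseline-adjusted ANCOVA on the observed scores gives 0.69 SD and baseline-carried-forward gives 0.38 SD. 0.38 / 0.69 = 0.55, the share observed, because dropouts are assigned no change.

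**Dependence on unseen outcomes.** With equal dropout in the arms, the overall difference is 0.55 × (observed difference) + 0.45 × (unseen difference). Each 1-point difference between arms in the mean of the unseen outcomes therefore moves the estimate by 0.45 points. In SD units, a 0.25 SD shift in ICT dropouts moves it by 0.45 × 0.25 = 0.11 SD and a 0.50 SD shift by 0.225 SD. An estimate near 0.70 SD becomes about 0.58 or 0.47 SD.

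**Informative dropout with no true effect.** If dropout depends on the unseen 1-month score in the ICT arm only (assumed logit slope 0.5 to 1.0 per SD), baseline-adjusted ANCOVA on the observed scores shows a false benefit of 0.16 to 0.30 SD and rejects in 11% to 31% of trials.

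**The case against.** Several objections carry weight.

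- **Nothing addresses dropout.** A reader might infer this, but it is too strong. Section {27d} allows a look at dropout patterns and {27b} adds a completer analysis. However, the first is optional and uses observed characteristics only, and the second uses completers only. Neither varies the assumption about unseen scores.
- **The rule cannot be carried out.** This is also too strong. Amount, timing, pattern, relation to baseline and recorded reasons such as early discharge are all observable. Only dependence on the unseen score is not. The rule is incomplete and applied after the fact, but it is not impossible.
- **The trial will have a 20% to 30% false-positive rate.** The protocol does not support this. It names no single-imputation method, and three of the five methods tabulated hold the error rate near 5%. The high rates belong to methods that {27c} leaves open but does not select.
- **The 45% is not this trial's rate.** Correct. It is a planning figure from another study at the centre, and sections {15b}, {15c} and {25b} plan reminders and follow-up of early leavers.
- **The 2.37-point change in section {19} as a yardstick.** It should not be used as one. It is 3.44 − 1.07, a pre–post change within one treated group, and the protocol states no between-arm effect in points.
- **Oversight exists.** Section {3d} requires consent of all seven Doctoral Committee members for relevant trial decisions, and {27c} does not itself say who picks the method. Consent given after data collection does not make the choice prespecified.

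A journal article may leave detail to a fuller plan. Here, though, {27c} states a rule, and {5} says that the analysis plan is in this document.

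**Conclusion.** The point stands. The protocol fixes the timing of the missing-data decision badly: after data collection, in a trial whose only analyst is unblinded, for a primary outcome that may be about 45% missing. It states no sensitivity analysis under informative dropout.

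The size is illustrative. Methods left open by {27c} give false-positive rates from about 5% to about 30% under the stated assumptions, and one of them cuts a true effect to about 55%. The 0.45-point movement per point of unseen difference is plain arithmetic, but it assumes 45% missing in both arms and scales with the actual rate. If far fewer are lost, the problem shrinks in proportion.

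This should be corrected before analysis, because the superiority claim in section {12} rests on this step.

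**What to change.** Replace the sentence in {27c}, before any outcome data are examined by arm, with a fixed rule:

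1. **One named primary method under missing-at-random.** For example, a likelihood-based repeated-measures model on all randomized participants, using every observed OAS-M visit, with the between-arm contrast at 1 month as the estimate. Name one method, not a choice of several.
2. **No single imputation treated as observed data.**
3. **One delta-adjusted sensitivity analysis.** Shift the unseen ICT values unfavourably over a range fixed in advance (0, 0.25 and 0.50 SD would serve as an example). Report it whether or not the primary result is significant.
4. **Dropout and its reasons tabulated by arm in every case,** in place of the conditional wording in {27d}. Include withdrawals of consent, whose data section {15b} removes although {27b} promises all randomized participants.

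The amendment should be dated and should state that no comparison by arm has yet been made. Enrolment is expected to run to December 2026 and no interim analysis is planned, so there is still time. The cost is a protocol amendment through the Doctoral Committee, ethics committee and registry, some extra analysis, and a conclusion that may look less firm. No new data are needed.
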